#### 4.7.2 t0: Baseline data collection and randomization

1. Once the data of a new study participant has been received, the study team at the Charité is automatically informed and a study nurse takes over the care of this study participant.
2. The study nurse should contact the study participant within 1-2 weeks after inclusion.
3. To collect baseline data, the study nurse conducts a computer-assisted telephone interview (CATI) with the study participant. If this is not possible due to limitations on the part of the participant, the baseline data collection can, as an exception, also be carried out by the study nurse during a home visit, at the Charité or during a practice visit.
4. After completion of baseline data collection, the study nurse randomly assigns subjects to a study arm.
5. If study participants are assigned to the intervention arm, the study nurse will arrange the first appointment with the link worker within 7 days of randomization if possible. If study participants are assigned to the control arm, she will send the study participant the brochure with local support services.

|                                  |                                   |                                                                                                         |                  |
|----------------------------------|-----------------------------------|---------------------------------------------------------------------------------------------------------|------------------|
| Version: V1.2                    | Last review:
February 12, 2025 | Created: [name], [name], [name], [name], [name] | Page
28 of 52 |
|                                  |                                   | Reviewed by: [name], [name]                                                    |                  |
| Release on:
February 12, 2025 | Next check:
N/A                | Released: [name]
Valid from: 04.09.2024                                             |                  |

|                |                          |                                                              |  |
|----------------|--------------------------|--------------------------------------------------------------|--|
| study protocol | Study: „Soziales Rezept“ | Campus:
CCM                                               |  |
|                |                          | Scope:
Institute for General Practice and Family Medicine |  |

The details of the procedures at  $t_0$  are described in detail in the *SocPres\_SOP data collection*.

#### 4.7.3 $t_1$ follow-up survey after three months

The first follow-up survey will take place no earlier than three months after the randomization of the study participant. It will be conducted by the study nurse as a CATI or, in exceptional cases, during a home visit, at the Charité or during a doctor's office visit. The survey will take place as soon as possible at the three-month appointment, but no later than four months after randomization.

The details of the processes at  $t_1$  are described in detail in the *SocPres\_SOP data collection*.

#### 4.7.4 $t_2$ Follow-up survey after six months

The second follow-up survey will take place at least six months after the randomization of the study participant. It will be conducted by the study nurse again as a CATI or, in exceptional cases, during a home visit, at the Charité or during a doctor's office visit. The survey will take place as soon as possible at the six-month appointment, but no later than seven months after randomization.

The details of the processes at  $t_2$  are described in detail in the *SocPres\_SOP data collection*.

### 4.8 Medical care

The medical care of the participants by their family doctors remains unaffected by randomization into one of the two study arms and is provided without any restrictions throughout the entire period of the study.

## 5 termination criteria

### 5.1 termination criteria for individual study participants

1. Study participants can terminate their participation in the study at any time without giving reasons.
2. Investigators may stop the study for a participant if the risk to that person outweighs the individual benefit.

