| Goals                                                                                                          | endpoints                                                                                                                                          |
|----------------------------------------------------------------------------------------------------------------|----------------------------------------------------------------------------------------------------------------------------------------------------|
| main goal                                                                                                      | Primary endpoints                                                                                                                                  |
| Determination of the feasibility and feasibility of a randomized controlled trial on the "social prescription" | Proportion of participants who have at least one appointment with the link worker (intervention arm only, within 6 months)                         |
|                                                                                                                | Proportion of participants who discontinue the study before 6 months of follow-up (discontinuation rate, both arms)                                |
| Secondary goals                                                                                                | Secondary endpoints                                                                                                                                |
| Determination of Acceptance                                                                                    | Satisfaction of GPs (questionnaire after last patient last visit for all participating GPs )                                                       |
|                                                                                                                | participant satisfaction (3 -month follow-up and 6-month follow-up)                                                                                |
| Determination of practicality                                                                                  | Estimated time expenditure of the general practitioners (questionnaire after last patient last visit for all participating general practitioners ) |

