### 8.2 case number estimate

Since this is an exploratory feasibility study without confirmatory hypothesis testing, no formal sample size calculation will be performed. Based on previous experience, we assume that the analysis of a total of 215 participants (in a ratio of 2:1: 143 in the SP arm and 72 in the TAU+ arm) is sufficient to descriptively determine the feasibility and acceptability aspects of the study and to obtain further information for planning the subsequent study.

A drop-out of approximately 30% is expected, so that follow-up data for secondary clinical endpoints of 150 patients (n = 100 in the SP arm and n = 50 in the TAU+ arm) will be available after 6 months.

|                                  |                                   |                                                                                                         |                  |
|----------------------------------|-----------------------------------|---------------------------------------------------------------------------------------------------------|------------------|
| Version: V1.2                    | Last review:
February 12, 2025 | Created: [name], [name], [name], [name], [name] | Page
33 of 52 |
|                                  |                                   | Reviewed by: [name], [name]                                                    |                  |
| Release on:
February 12, 2025 | Next check:
N/A                | Released: [name]                                                                       |                  |
|                                  |                                   | Valid from: 04.09.2024                                                                                  |                  |

|                   |                          |                                                                 |  |
|-------------------|--------------------------|-----------------------------------------------------------------|--|
| study
protocol | Study: „Soziales Rezept“ | Campus:
CCM                                                  |  |
|                   |                          | Scope:
Institute for General Practice and
Family Medicine |  |

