### 8.3 evaluation populations

Analyses using the Full Analysis Set (FAS) are performed according to the intention - to - treat principle with all available data (missing data are not imputed).

The per-protocol population is defined as patients who adhere to the protocol (details are defined in the SAP).

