### 8.4 analyses

Primary endpoints: The proportion of participants in the intervention group who attended at least one appointment with the link worker and the proportion of participants who discontinued the study before the 6-month follow-up (dropout rate) will be analyzed descriptively, with frequencies and percentages, including 95% confidence intervals per treatment group. The comparison of the dropout rate between the treatment groups will be done descriptively and using logistic regression to determine possible influencing factors.

Secondary endpoints are analyzed descriptively (frequencies/percentages, mean/standard deviation or median/interquartile depending on scale and distribution, each with corresponding 95% confidence intervals).

Comparisons between treatment groups will be performed using logistic regression (binary endpoints) or analysis of covariance (continuous endpoints adjusted for baseline , if available), taking center into account.

Safety: Adverse events are analyzed descriptively (frequencies and percentages per treatment group).

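### Section 5.1 gives one response to individual risk, stopping the study, and so selectively loses scheduled outcome and safety data and mixes safety stops into the primary drop-out endpoint

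*Protocol*

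**What the plan says.** Section 5.1 of the protocol contains two rules for individuals, both at the level of the study. For the participant: "Study participants can terminate their participation in the study at any time without giving reasons". For the investigator: "Investigators may stop the study for a participant if the risk to that person outweighs the individual benefit". No other section says what data collection follows such a stop.

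Table 2 in section 3 defines the second primary endpoint as "Proportion of participants who discontinue the study before 6 months of follow-up (discontinuation rate, both arms"). The synopsis labels the same quantity loss to follow-up, and section 8.4 calls it the dropout rate: "the proportion of participants who discontinued the study before the 6-month follow-up (dropout rate) will be analyzed descriptively". None of these places separates participants by reason for leaving or by who took the decision.

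Table 4 schedules a safety assessment (row 'Security') at baseline, at the link-worker sessions and at the 3- and 6-month surveys (t1 and t2). Section 8.3 analyses by the "intention - to - treat principle with all available data (missing data are not imputed").

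Section 14.4 names two burdens. Time spent applies to both arms. Emotional upset and possible decompensation from conversations with the link worker apply to the intervention group.

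**The concern.** The named risk attaches to the intervention contact, but the written response attaches to the whole study. An investigator who follows 5.1 as written for a participant distressed by the conversations also ends that person's outcome interviews.

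Two things are at stake. First, the loss is selective. The people whose later WHODAS scores and scheduled safety assessments disappear are those judged to be at risk, and they will probably be in one arm. With no imputation, nothing in the planned analysis compensates. An analysis plan can decide how to count these people, but it cannot recover interviews that were never held, so the matter belongs in the protocol.

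Second, the drop-out endpoint exists to tell the planners of a confirmatory trial how many participants are lost, with particular interest in the control group (sections 2 and 4.2). A safety decision by the GP and a participant's unwillingness to be followed are different quantities. On the current wording they fall into one proportion, which section 8.4 then compares between arms.

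**Working it through.** **Step 1: the plan's own figures.** Inputs from section 8.2: 215 randomized ("in a ratio of 2:1: 143 in the SP arm and 72 in the TAU+ arm") and "A drop-out of approximately 30% is expected, so that follow-up data for secondary clinical endpoints of 150 patients".

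- Total: 215 × 0.70 = 150.5, stated as 150.
- SP: 143 × 0.70 = 100.1, stated as 100.
- TAU+: 72 × 0.70 = 50.4, stated as 50.

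The figures reproduce. There is no arithmetic error in the plan.

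**Step 2: precision of the drop-out endpoint.** Expected drop-outs are 143 − 100 = 43 in SP and 72 − 50 = 22 in TAU+. With Wilson 95% intervals:

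| Arm | Expected drop-out | 95% CI | Half-width |
|---|---|---|---|
| SP | 43/143 = 30.1% | 23.2 to 38.0 | about 7 points |
| TAU+ | 22/72 = 30.6% | 21.1 to 42.0 | about 10 points |

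**Step 3: effect of each investigator stop counted as drop-out.**

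- SP: 1/143 = 0.70 points.
- TAU+: 1/72 = 1.39 points.

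The protocol gives no expected number of stops. One to five per arm is an assumption.

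- SP: 1/143 to 5/143 = 0.7 to 3.5 points.
- TAU+: 1/72 to 5/72 = 1.4 to 6.9 points.

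The expected 30% may already include such stops. If it does, keeping one to five of these people in follow-up lowers the SP rate from 30.1% to between 42/143 = 29.4% and 38/143 = 26.6%, and the TAU+ rate from 30.6% to between 21/72 = 29.2% and 17/72 = 23.6%. If the stops come on top, the SP rate rises to between 44/143 = 30.8% and 48/143 = 33.6%. Either way the shift lies inside the half-widths of Step 2.

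**Step 4: which data a stop removes, on the plain wording.**

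- *Surveys at t1 and t2* (sections 4.7.3 and 4.7.4): these are study procedures, so stopping the study for a person ends them. This includes WHODAS 2.0 at 6 months, which the synopsis names as the main clinical endpoint.
- *Safety assessments at t1 and t2* (Table 4): lost with the surveys.
- *GP reporting of adverse events* (sections 6.1.5 and 13.1.2): not stated. The route runs through the GP within seven days and has no end date tied to individual termination. Recorded events are followed to final evaluation (section 13.1.3), and GP care continues regardless of the study arm (section 4.8). Reporting can continue, but nothing requires it to.

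**The case against.** The strongest reply is that silence in 5.1 is being read as a set of consequences. Several stronger readings are tempting, and the documents do not support them.

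- *A stopped participant leaves adverse-event collection, so SP will look safer than it is.* A reader might infer this, but no section says so. The GP route described in sections 4.8, 6.1.5, 13.1.2 and 13.1.3 can carry on, and a named SOP that is not shown may govern it. Only the loss of the assessments scheduled at t1 and t2 follows from the wording.
- *Link-worker contact cannot end without leaving the study.* This is wrong for the protocol as a whole. Section 4.3 leaves the number and duration of appointments open, so contact can end after any session. Table 2 has separate endpoints for attending an appointment and for discontinuing the study. Section 5.1 is also permissive.
- *Section 5.1 contradicts the intention-to-treat analysis in 8.3.* It does not. That analysis uses the data available, and a stopped participant stays in the allocated arm with the data collected up to then.
- *Stops will be numerous.* Section 12.2 rates the risk of adverse events as very low, and section 14.4 says that such effects were not reported in earlier studies. Even ten SP stops (10/143 = 7.0 points) would be an unsourced figure that sits badly with those statements.

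The reply also holds that classifying reasons for drop-out is ordinary work for the analysis plan. That is fair for tabulation. It does not settle whether the interviews take place. What remains is that the one response written down for risk is a study-level stop, and that following it removes scheduled data from the people in whom those data matter most.

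**Conclusion.** The point holds in limited form. Section 5.1 does not separate ending the intervention from leaving the study. Followed as written, it produces selective loss of 3- and 6-month outcomes and of the safety assessments scheduled with them, and it places safety-driven stops in the primary drop-out endpoint. Continuation of GP adverse-event reporting after a stop is undefined; it has not been shown to end.

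The numerical effect is small: 0.7 points per SP stop and 1.4 per TAU+ stop. One to five SP stops give 0.7 to 3.5 points against a half-width of about 7. The conclusion rests on the selectivity of the loss. In a low-risk intervention, one or two affected people without follow-up matter more for the safety account than for the drop-out rate.

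Three assumptions are involved: that stopping the study is read in its ordinary sense, that one to five stops is a reasonable range, and that stops fall mainly in SP because the named non-time risk is specific to that arm. Section 5.1 itself applies to both arms. This is an inexpensive improvement that should be made. It is not an error that undermines the study.

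**What to change.** Reconcile section 5.1 with the endpoint wording in the synopsis, Table 2 and section 8.4, with Table 4, and with section 13.1:

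1. Record end of link-worker contact (date, reason, who decided) as a status separate from end of study participation.
2. State that the t1 and t2 surveys and adverse-event reporting continue after the former unless the participant withdraws consent to data collection.
3. Count only end of study participation in the primary drop-out endpoint, and report investigator-initiated stops separately by arm.
4. Use one label for that endpoint in place of the present three.

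When contact or participation should end remains for the investigator and the sponsor to define; nothing here proposes a clinical criterion.

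The cost is a few sentences, one status field in the eCRF, and a few more interviews with participants who have stopped the intervention. No new visits are needed.

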### 5.2 Termination criteria for parts of the study or the entire study

1. In case of repeated violations of the trial plan (e.g. allocation), the sponsor representative can close individual trial centers.

|                                  |                                   |                                                                                                         |                  |
|----------------------------------|-----------------------------------|---------------------------------------------------------------------------------------------------------|------------------|
| Version: V1.2                    | Last review:
February 12, 2025 | Created: [name], [name], [name], [name], [name] | Page
29 of 52 |
|                                  |                                   | Reviewed by: [name], [name]                                                    |                  |
| Release on:
February 12, 2025 | Next check:
N/A                | Released: [name]
Valid from: 04.09.2024                                             |                  |

|                |                          |                                                              |  |
|----------------|--------------------------|--------------------------------------------------------------|--|
| study protocol | Study: „Soziales Rezept“ | Campus:
CCM                                               |  |
|                |                          | Scope:
Institute for General Practice and Family Medicine |  |

- The Data Safety and Monitoring Board (DSMB, see below) may recommend stopping recruitment of participants for either all or some treatment groups and/or some subgroups of participants. The sponsor representative decides on termination.

## 6 data collection

### 6.1 data sources

#### 6.1.1 Personally Identifiable Data

by the family doctors are securely transferred to the Charité by the practice staff.

#### 6.1.2 health data

The trial centers also collect and transmit other health data of the participants (long-term diagnoses, reason for the social prescription).

#### 6.1.3 survey data from family doctors

After the end of the study at the respective trial center, the participating general practitioners will be surveyed via online questionnaire.

#### 6.1.4 recruitment list

The information relevant to the feasibility endpoints in the recruitment lists completed by the investigators is regularly queried by the Charité.

#### 6.1.5 Adverse events

Adverse events are reported by the GP to the study team within seven days. Various secure transmission channels are available for this purpose, which are described in more detail in the associated SOP *SocPres\_SOP Reporting, evaluation and handling of adverse events* . Adverse events are stored in a central database (see Adverse events ).

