|                                            | consultation in the practice | baseline survey/randomization | First Link Worker Session | Follow up Link Worker sessions                        | 3-month follow-up | 6-month follow-up |
| inclusion                           |                              |                               |                           |                                                       |                   |                   |
| review of inclusion and exclusion criteria | X                            |                               |                           |                                                       |                   |                   |
| enlightenment                              | X                            |                               |                           |                                                       |                   |                   |
| consent                                    | X                            |                               |                           |                                                       |                   |                   |
| Sociodemographic data                      |                              | X                             |                           |                                                       |                   |                   |
| randomization                              |                              | X                             |                           |                                                       |                   |                   |
| treatment per study arm             |                              |                               |                           |                                                       |                   |                   |
| TAU+ (brochure)                            |                              | X                             |                           |                                                       |                   |                   |
| Social prescribing                         |                              | X                             | X                         | X                                                     | X                 | X                 |

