|                                  |                                   |                                                                                                         |                  |
|----------------------------------|-----------------------------------|---------------------------------------------------------------------------------------------------------|------------------|
| Version: V1.2                    | Last review:
February 12, 2025 | Created: [name], [name], [name], [name], [name] | Page
25 of 52 |
|                                  |                                   | Reviewed by: [name], [name]                                                    |                  |
| Release on:
February 12, 2025 | Next check:
N/A                | Released: [name]                                                                       |                  |
|                                  |                                   | Valid from: 04.09.2024                                                                                  |                  |

|                   |                          |                                                                 |  |
|-------------------|--------------------------|-----------------------------------------------------------------|--|
| study
protocol | Study: „Soziales Rezept“ | Campus:
CCM                                                  |  |
|                   |                          | Scope:
Institute for General Practice and
Family Medicine |  |

|                          |  |   |   |   |   |   |
|--------------------------|--|---|---|---|---|---|
| Subjective health status |  | X |   |   | X | X |
| Security                 |  | X | X | X | X | X |

|                                  |                                   |                                                                                                         |                  |
|----------------------------------|-----------------------------------|---------------------------------------------------------------------------------------------------------|------------------|
| Version: V1.2                    | Last review:
February 12, 2025 | Created: [name], [name], [name], [name], [name] | Page
26 of 52 |

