*Utilization behavior (relevant sections from PECUNIA RUM or EHIS- GeDA ) :* The PECUNIA instrument for measuring resource utilization (PECUNIA RUM) measures resource utilization in all sectors of the adult population that are relevant for cost calculation from a societal perspective: health and social care, education, (criminal) justice, productivity losses and informal care (30,31) . In the present study, selected items from this measurement instrument are used that relate to the topics

|                                  |                                   |                                                                                                         |                  |
|----------------------------------|-----------------------------------|---------------------------------------------------------------------------------------------------------|------------------|
| Version: V1.2                    | Last review:
February 12, 2025 | Created: [name], [name], [name], [name], [name] | Page
32 of 52 |
|                                  |                                   | Reviewed by: [name], [name]                                                    |                  |
| Release on:
February 12, 2025 | Next check:
N/A                | Released: [name]
Valid from: 04.09.2024                                             |                  |

|                |                          |                                                              |  |
|----------------|--------------------------|--------------------------------------------------------------|--|
| study protocol | Study: „Soziales Rezept“ | Campus:
CCM                                               |  |
|                |                          | Scope:
Institute for General Practice and Family Medicine |  |

examined in the study on health and social care, as well as in the context of productivity losses, in particular hospital stays and inpatient care facilities, emergency care, outpatient health services and social services, medication, informal care, incapacity for work. If possible, the culturally adapted version of EHIS- GeDA for Germany is used.

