### 13.1.2 reporting of adverse events

Adverse events are reported using the form *SocPres\_ReportingFormEvents* via secure communication channels by the investigators to the study management within 7 days of becoming known. The exact procedure is specified in the *SOP SocPres\_SOP : Reporting, evaluation and handling of adverse events*.

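### Table 4 schedules safety recording at link-worker sessions that only the intervention arm has, while the reporting text names only the GP; the passages need reconciling before events are compared by arm

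*Protocol*

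**What the plan says.** **Reporting text.** Section 6.1.5 says: "Adverse events are reported by the GP to the study team within seven days". Section 13.1.2 has events reported "by the investigators to the study management within 7 days of becoming known". Section 6.1.7 has link workers record what was discussed, which offers were made and how long the consultation lasted; adverse events are not named. Section 6.2 gives doctors' letters and practice software as the source data for events.

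**Visit schedule.** In Table 4 (section 4.7) the safety row reads "Security | | X | X | X | X | X": blank at t-1, marked at t0, at both session columns, and at t1 and t2. The first session column is headed "First Link Worker Session". Under section 4.3 only intervention participants see a link worker, with 2-5 appointments expected, and their GPs receive a feedback form afterwards.

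**Analysis.** Section 8.4: "Adverse events are analyzed descriptively (frequencies and percentages per treatment group". Separately, Table 2 and section 6.4 provide for utilisation items asked in both arms at baseline, t1 and t2, including "hospital stays and inpatient care facilities, emergency care".

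**Interviewers.** Section 4.7.2: "After completion of baseline data collection, the study nurse randomly assigns subjects to a study arm". Of the t2 survey, section 4.7.4 says: "It will be conducted by the study nurse again as a CATI". Section 4.5.2 rules out blinding of investigators, link workers, patients and the statistical analyses. It does not mention interviewers.

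**The concern.** Table and text disagree on where safety is captured and by whom, and either reading leaves a gap.

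- If sessions feed reporting, one arm has extra occasions on which an event can come to light, and section 8.4 then sets the two arms' percentages side by side.
- If they do not, the session marks in the safety row have no function, and this protocol does not say what happens to an event disclosed to a link worker.

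The events most exposed are those that need not leave a document. Section 13.1.1 defines suicidality to include thoughts and ruminations, and section 14.4 itself considers that the conversations could be upsetting. Deaths, emergency visits and admissions usually generate letters and are less exposed.

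The comparison has uses. Section 13.1 aims to demonstrate safety and section 16 plans a safety publication. Under sections 13.2 and 13.3, reported events go to a monitoring board that may recommend stopping recruitment to some treatment groups. An excess produced by detection alone would be read as a harm of the intervention.

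**Working it through.** **1. The plan's own figures.** 150 / (1 - 0.30) = 214.3, rounded up to 215. Retention: 215 x 0.7 = 150.5; 143 x 0.7 = 100.1; 72 x 0.7 = 50.4. The stated 215 (143/72) and 150 (100/50) reproduce. About 215 - 150 = 65 participants are expected to have no 6-month interview.

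**2. The passages side by side.**

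| Place | Who captures or reports safety |
|---|---|
| Table 4, safety row | t0, every session, t1, t2; no person named |
| 6.1.5, 13.1.2 | GP/investigator |
| 6.1.7 (link workers) | adverse events not listed |
| 4.3 | feedback to the GP, intervention arm only |
| 8.4 | percentages per arm, no split by source |

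No passage connects the session marks to a reporter.

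**3. Scheduled safety contacts after randomisation, if Table 4 is taken literally.** Control: t1 and t2 = 2. Intervention: 2 + (2 to 5) = 4 to 7, that is 2 to 3.5 times as many.

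**4. Size, on assumptions only.** The protocol gives no capture rates. Let d be the share of true events caught by routes both arms have, and s the share of the remainder elicited at sessions. With the same true risk in both arms, the observed ratio is

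R = [1 - (1 - d)(1 - s)] / d = 1 + (1 - d)s/d.

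- *GP route only* (d = 0.5 to 0.7, s = 0.25 to 0.5, true risk 20%). With d = 0.5 and s = 0.5: 15% vs 10%, R = 1.50. With d = 0.7 and s = 0.25: 15.5% vs 14%, R = 1.11.
- *Adding t1/t2*, assumed to recover a share t = 0.5 to 0.8 of what the GP missed, in both arms, so d = 1 - (1 - g)(1 - t), where g is the GP share. With g = 0.5, t = 0.5, s = 0.5: d = 0.75, R = 1 + 0.25 x 0.5/0.75 = 1.17. With g = 0.7, t = 0.8, s = 0.25: d = 0.94, R = 1 + 0.06 x 0.25/0.94 = 1.02.
- *Per-session version*: each of k = 2 to 5 sessions finds a missed event with probability c = 0.1 to 0.2, so s = 1 - (1 - c)^k = 0.19 to 0.67. With d = 0.5 to 0.9, R runs from 1.02 to 1.67. The top needs all common routes together to miss half the events.

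The answer follows the assumed inputs, so no single figure can be claimed.

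**5. Interviewers.** In section 4.7.2 one nurse takes over the participant, interviews, allocates, then books the link worker or sends the brochure. Sections 4.7.3 and 4.7.4 give t1 and t2 to the study nurse. No masked interviewer is provided.

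**The case against.** The text names the GP as reporter in both arms, and the only evidence for capture at sessions is the marks in one table row. Marks in Table 4 are used loosely: the social prescribing row is also marked at t0, t1 and t2, which are survey points. Link-worker documentation and event reporting are referred to SOPs that are not shown. Emergency visits and admissions have documentary sources, and a between-arm comparison of utilisation is already planned in Table 2 and section 11. The trial is open and exploratory, and section 4.5.1 says randomisation is not meant to test comparative hypotheses.

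Much of this stands, and it rules out three stronger readings that a reader might infer:

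- *Events are collected and reported by link workers.* The protocol does not say so; the table only makes it possible. Nor can one say that no route exists for events disclosed to them, since the SOPs may contain one.
- *The safety comparison is inflated by 1.1 to 1.5.* That range leaves out the t1/t2 contacts, which Table 4 gives to both arms, and rests on invented capture rates.
- *Patient-reported outcomes suffer arm-dependent ascertainment by the nurse who randomised the participant.* The schedule, mode and shared instruments are the same in both arms, so the issue is unblinded interviewing. That the same individual calls again is implied but not stated, and section 6.1.6 speaks of nurses in the plural. Participants know their arm and report for themselves, so a masked interviewer would remove only part of any bias.

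The contradiction remains. An SOP cannot make two protocol passages agree, and an exploratory label does not make per-arm percentages comparable when detection may differ.

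**Conclusion.** The point holds as an inconsistency that creates a risk of unequal detection. Table 4 places safety recording at sessions only one arm attends; sections 6.1.5, 6.1.7 and 13.1.2 do not provide for it; and section 8.4 compares the arms without separating sources.

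If session disclosures feed reporting, the exposure falls mainly on suicidality and other events, and less on documented emergency visits and admissions. The size is unknown. For the assumed GP capture of 50-70%, 1.1-1.5 is an upper illustration that ignores t1/t2, and about 1.02-1.17 results when these interviews recover 50-80% of missed events. Other assumptions give other values. If session disclosures do not feed reporting, the table is wrong and the bias through that path does not arise.

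The interviewer issue is secondary: an unstated limitation on the between-arm comparison of the main clinical endpoint, WHODAS 2.0 at 6 months, and of the other patient-reported outcomes.

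**What to change.** 1. Reconcile Table 4 with sections 6.1.5, 6.1.7 and 13.1.2: state who records and who reports safety at the link-worker sessions, and likewise at t1 and t2.
2. Record the source of each event: GP, GP prompted by a link worker, session, or interview.
3. In section 8.4, base the between-arm comparison on sources common to both arms: the t1/t2 answers on emergency care and hospital stays, alongside GP reports not triggered by a link worker. List session-detected events separately. Check that the hospital items separate unplanned from planned stays, because section 13.1.1 counts only unplanned ones. These items do not cover suicidality, for which unprompted GP reports are the common source.
4. In section 4.5.2, say that t1/t2 interviewers are not blinded and note this as a limitation. Ask the generic outcome measures before the goal-based outcome and the satisfaction items.

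**Cost.** One clarified reporting line, one source field, analysis wording and a fixed question order. The drawback is that interview data miss drop-outs, about 30%, so GP-reported events must still be shown for all randomised participants.

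Having a different nurse make the t1/t2 calls is optional. Staffing is not described, the gain in masking is partial, and a change of contact person could affect drop-out, which is a primary endpoint.
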